**Version 2; 22.6.2004**

**CONFIDENTIAL**

## 1. INTRODUCTION AND BACKGROUND

### 1.1 The need for new vaccine against tuberculosis

Tuberculosis (TB) kills about three million people annually. It is estimated that one third of the world's population are latently infected with *Mycobacterium tuberculosis* (*M.tb*). Multi-drug resistant strains of *M.tb*, and co-infection with *M.tb* and HIV present major new challenges. The currently available vaccine, *M. bovis* BCG, is largely ineffective at protecting against adult pulmonary disease in endemic areas and it is widely agreed that a new more effective tuberculosis vaccine is a major global public health priority. However, it may be unethical and impractical to test and deploy a vaccine strategy that does not include BCG, as BCG does confer worthwhile protection against TB meningitis and leprosy. An immunisation strategy that includes BCG is also attractive because the populations in which this vaccine candidate will need to be tested will already have been immunised with BCG.

*M.tb* is an intracellular organism. CD4+ Th1-type cellular responses are essential for protection and there is increasing evidence from animal and human studies that CD8+ T cells also play a protective role. However, it has generally been difficult to induce strong cellular immune responses in humans using subunit vaccines. DNA vaccines induce both CD4+ and CD8+ T cells and thus offer a potential new approach to a TB vaccine. DNA vaccines encoding various antigens from *M. tuberculosis* have been evaluated in the murine model, and to date no DNA vaccine alone has been shown to be superior to BCG.

A heterologous prime-boost immunisation strategy involves giving two different vaccines, each encoding the same antigen, several weeks apart. Such regimes are extremely effective at inducing a cellular immune response. Using a DNA- prime/MVA-boost immunisation strategy induces high levels of CD8+ T cells in animal models of malaria and HIV, and high levels of both CD4+ and CD8+ T cells in animal models of TB. BCG immunisation alone induces only CD4+ T cells in mice. A prime-boost strategy using BCG as the prime and a recombinant MVA encoding an antigen from *M.tb* that is also present in BCG (antigen 85A: 'MVA85A') as the boost, induces much higher levels of CD4+ T cells than BCG or MVA85A alone. In addition, this regime generates specific CD8+ T cells that are undetectable following immunisation with BCG alone.

### 1.2 Recombinant viruses as vaccines.

Recombinant viruses used alone have for some years represented a promising vaccine delivery system, particularly for inducing cellular immune responses. The recombinant virus encodes the immunising protein or peptide. Immunisation by a recombinant virus vaccine occurs when host cells take up and express the inoculated attenuated virus encoding a protective antigen. The expressed protein often has the native conformation, glycosylation, and other post-translational modifications that occur during natural infection. Recombinant viral vaccines may elicit both antibody and cytotoxic T-lymphocyte responses, which persist without further immunisations. Many viruses have been investigated as potential recombinant vaccines. The successful worldwide eradication of smallpox via vaccination with live vaccinia virus highlighted vaccinia as a candidate for recombinant use. The recognition in recent years that non-replicating strains of poxvirus such as MVA and avipox vectors can be more immunogenic than traditional replicating vaccinia strains has enhanced the attractiveness of this approach. MVA (modified

vaccinia virus Ankara) is a strain of vaccinia virus which has been passaged more than 570 times through avian cells, is replication incompetent in human cell lines and has a good safety record. It has been administered to more than 120,000 vaccinees as part of the smallpox eradication programme, with no adverse effects, despite the deliberate vaccination of high risk groups. This safety in man is consistent with the avirulence of MVA in animal models. MVA has six major genomic deletions compared to the parental genome severely compromising its ability to replicate in mammalian cells. Viral replication is blocked late during infection of cells but importantly viral and recombinant protein synthesis is unimpaired even during this abortive infection. Replication-deficient recombinant MVA has been seen as an exceptionally safe viral vector. When tested in animal model studies recombinant MVAs have been shown to be avirulent, yet protectively immunogenic as vaccines against viral diseases and cancer. The most useful data on the safety and efficacy of various doses of a recombinant MVA vaccine comes from clinical trial data with a recombinant MVA expressing a number of CTL epitopes from *Plasmodium falciparum* pre-erythrocytic antigens fused to a complete pre-erythrocytic stage antigen, Thrombospondin Related Adhesion Protein (TRAP). These trials have given a total of 169 immunisations with this recombinant MVA, to 49 UK vaccinees 38 Gambian vaccinees (20 of whom were children aged 1-5). 6 doses of  $1 \times 10^7$  pfu, 139 doses of  $5 \times 10^7$  pfu, 6 doses of  $1 \times 10^8$  pfu and 18 doses of  $2.5 \times 10^8$  pfu have been administered, all without serious adverse effects.

### 1.3 Recombinant MVA encoding antigen 85A

Secreted antigens from *M. tuberculosis* are released from actively metabolising bacteria, and are important targets in protective immunity. Antigen 85A is a major secreted antigen from *M. tuberculosis* which forms part of the antigen 85 complex (A, B and C). This complex constitutes a major portion of the secreted proteins of both *M.tb* and BCG. It is involved in fibronectin binding within the cell wall and has mycolyltransferase activity.

MVA85A induces both a CD4+ and a CD8+ epitope when used to immunise mice. When mice are primed with BCG and then given MVA85A as a boost, the levels of CD4+ and CD8+ T cells induced are higher than with either BCG or MVA85A alone.

We are evaluating the safety and immunogenicity of the following 3 groups:

1. BCG alone
2. MVA85A alone
3. BCG prime-MVA85A boost

BCG-BCG provides a control group for BCG-MVA85A. Many countries have a tradition of repeated BCG vaccination and the criteria for revaccination differ between countries.

## 2. DESCRIPTION OF THE STUDY

### 2.1 Study Objective

To assess the safety and immunogenicity of BCG delivered intradermally into the deltoid region in volunteers who have received BCG 10 - 20 years previously.

## **2.2 Selection of volunteers**

Volunteers for the study will be recruited through advertisements. Each volunteer will have received an information sheet concerning the study and will have agreed to participate in writing. Volunteers will be given at least 48 hours between reading the information leaflet and agreeing to participate. Female volunteers will be told of the theoretical risk of congenital anomaly should they become pregnant during the study and only those who undertake to take precautions to avoid pregnancy during the study period will be eligible. Volunteers will give signed consent for their GP's to be notified about their participation in the trial. The GP will be faxed a letter on the day of screening and asked to reply if they know of a reason why the volunteer should not take part. The signed consent form will also be faxed with the letter.

## **2.3 Screening**

Volunteers will be asked to sign the informed consent form for screening. The following will be performed:

- Medical history and examination
- Laboratory evaluations – including clinical chemistry, haematology, HLA typing, anti-HBV antibodies, anti-HCV antibodies, anti-HIV antibodies
- Heaf test – to exclude prior exposure to TB
- Urinalysis and urine pregnancy test if female

## **2.4 Inclusion Criteria**

- Healthy adult aged 18-55 years.
- Normal medical history and physical examination.
- Normal urine dipstick, blood count, liver enzymes, and creatinine.

## **2.5 Exclusion Criteria**

- a. Exposure to TB at any point. A positive ESAT6/CFP10 Elispot response (defined as greater than 5 spots/well above background and at least double the background response).
- b. Clinically significant history of skin disorder (eczema, psoriasis, etc.), allergy, immunodeficiency, cardiovascular disease, respiratory disease, endocrine disorder, liver disease, renal disease, gastrointestinal disease, neurological illness, psychiatric disorder, drug or alcohol abuse.
- c. Oral or systemic steroid medication or the use of immunosuppressive agents.
- d. Positive HIV antibody test, HCV antibody test or positive HBV serology except post-vaccination.
- e. Heaf test greater than Grade II
- f. Confirmed pregnancy

## **2.6 Withdrawal Criteria**

- a. Withdrawal of consent by subject for any reason

- b. Loss to follow-up
- c. Non-compliance with study procedures
- d. Protocol violation
- e. Serious adverse event (as defined in Appendix 3)
- f. Any other reason at discretion of the Principal Investigator
- g. Confirmed pregnancy during study period

## **2.7 Immunisation**

On Day 0, subjects will receive a single intradermal injection of 0.1ml BCG over the deltoid muscle. Vital signs will be monitored at 30 and 60 minutes post-immunisation. Local reactions at the site of administration will be evaluated at 60 minutes.

A photograph of the injection site may be taken at 48 hours (with written consent). The injection site will be reviewed 7 days after each immunization.

Blood will be taken at the following time points: At the screening visit\*, prior to the vaccination, 1 week after the first vaccination\*, 2 weeks, 4 weeks, 8 weeks, 12 weeks\* and 24 weeks after the vaccination. Up to 55 mls will be taken at any one time with the total being no more than 500 mls over the study period. \*Samples taken on these dates will be tested for full blood count and biochemical screen. Immunological assays will be performed at all time points to determine vaccine immunogenicity. A pregnancy test will be performed prior to vaccination for female volunteers. Peripheral blood mononuclear cells will be prepared for cellular immunological assays to be performed without or following cryopreservation. Other serological measures of immune response, i.e. antibody titres, will be assayed on frozen plasma samples.

All blood tests will be taken within 1-3 days of the due date as described in the schedule above.

At the 24 week timepoint, a Heaf test will be repeated in order to document the change (if any) in Heaf responsiveness after the second BCG vaccination.

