## **2.8 Endpoints**

The occurrence and severity of local side-effects

The occurrence and severity of systemic side-effects

The induction of T cell responses (as measured by an interferon-gamma Elispot assay).

Proliferation assays and cytotoxic T cell assays will be performed on strong CD4+ and CD8+ responses respectively.

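### The blood drawn just before vaccination is not tested for haematology and chemistry, so for the indices that decide entry the only pre-dose safety result is the one chosen to be normal

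*Protocol*

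**What the plan says.** Section 2.7 gives the sampling times as one list: screening, pre-vaccination, weeks 1, 2, 4, 8, 12 and 24. An asterisk stands on screening, week 1 and week 12 only, with the rule "Samples taken on these dates will be tested for full blood count and biochemical screen". The relevant part of the list reads "prior to the vaccination, 1 week after the first vaccination", and the asterisk belongs to the week 1 item, not to the pre-vaccination one.

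The pre-vaccination blood does have a use: "Immunological assays will be performed at all time points to determine vaccine immunogenicity". The only other pre-dose test that 2.7 names is for pregnancy: "A pregnancy test will be performed prior to vaccination for female volunteers".

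Screening (2.3) covers laboratory work "including clinical chemistry, haematology, HLA typing" and more. Entry (2.4) then requires "Normal urine dipstick, blood count, liver enzymes, and creatinine". No interval between screening and Day 0 is stated.

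Every participant is vaccinated: "subjects will receive a single intradermal injection of 0.1ml BCG over the deltoid muscle". Section 1.3 mentions other regimens under evaluation, but each of them contains a vaccine, and no concurrent unvaccinated group is described. Safety is half of the objective (2.1), and 2.8 lists "The occurrence and severity of systemic side-effects" among the endpoints.

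**The concern.** A sample that decides entry is a poor baseline for what it was selected on. Volunteers whose blood count, liver enzymes or creatinine were out of range that day are excluded, so the enrolled group starts at zero. At the next measurement nobody has been selected, and ordinary within-person variation carries some values outside the limits. With a single vaccinated arm, that rise appears only after BCG.

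Appendix 1 uses timing after vaccination as one criterion for relatedness, and a week 1 abnormality after a normal screen satisfies it. An investigator or reader then has no result from the day of dosing to show that the value had already moved. A later analysis plan can choose how to define baseline, but it cannot supply a Day 0 result that was never measured.

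**Working it through.** The plan states no laboratory abnormality rate, so there is no figure to reproduce. The check has two parts.

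**1. The schedule.** There are 8 draws, of which 3 are tested for haematology and chemistry. Of those 3, one precedes vaccination, and it is the eligibility sample.

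**2. Size of the chance rise, assuming no vaccine effect.** These assumptions are not in the protocol: each index is normally distributed, its limits are a two-sided 95% range (|z| > 1.96), and any two visits have the same within-person correlation ρ. Let b be the person's stable level and

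g(b) = Φ[(1.96 − √ρ·b)/√(1−ρ)] − Φ[(−1.96 − √ρ·b)/√(1−ρ)],

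the chance of being in range at one visit. Then

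- P(out at week 1 | in at screening) = ∫φ·g(1−g) / 0.95 = (0.05 − P(out at both visits)) / 0.95
- P(out at week 1 or 12 | in at screening) = ∫φ·g(1−g²) / 0.95
- share of week 1 out-of-range values already out at Day 0 = ∫φ·g(1−g)² / ∫φ·g(1−g)

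| ρ | P(out at both visits) | Screening | Week 1 | Week 1 or 12 | Already out at Day 0 |
|---|---|---|---|---|---|
| 0.4 | 0.0068 | 0% | (0.05−0.0068)/0.95 = 4.55% | 8.6% | 12% |
| 0.6 | 0.0125 | 0% | (0.05−0.0125)/0.95 = 3.95% | 7.2% | 19% |
| 0.8 | 0.0220 | 0% | (0.05−0.0220)/0.95 = 2.95% | 5.1% | 28% |

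Widening ρ to 0.3 and 0.9 gives 4.75% and 2.14% at week 1, hence about 2% to 5% per index.

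Under this model an untested Day 0 sample has the same out-of-range rate as week 1, so the expected group change from Day 0 is zero. If correlation fades with time the cancellation is partial. For example, with 0.8 between screening and Day 0 but 0.4 between screening and week 12, the spurious rise is 4.55 − 2.95 = 1.6 percentage points from Day 0, against 4.55 from screening.

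**3. What reaches Appendix 2.** In the Appendix 2 table as it stands in the public text, AST, ALT, GGT and alkaline phosphatase are graded upwards only, from 1.25 x ULN. Take ULN at z = 1.96, four independent tests, and selection on being at or below ULN at screening:

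- Above ULN at week 1: 1.44% (ρ = 0.8) to 2.22% (ρ = 0.4) per test. For any of four, 1 − (1−0.0144)⁴ = 5.6% to 1 − (1−0.0222)⁴ = 8.6%.
- Above 1.25 x ULN: the limit moves to z = 1.96 + ln(1.25)/SD. With an assumed log-scale SD of 0.25 this is 2.85, and with 0.45 it is 2.46. Per test the rate is 0.04% to 0.59%. For any of four it is about 0.2% to 2.3%.

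**4. Would counting only results worse than Day 0 be enough?** No. By the table, 72% to 88% of chance out-of-range values at week 1 were in range at Day 0 and would still count as new. Of the 12% to 28% already out, about half would by symmetry be further out at week 1, so such a rule removes only about 6% to 14%.

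**The case against.** The case on the other side is substantial, and most of it limits the size of the point.

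- **Large percentages do not describe adverse events.** A reader might infer that a third or more of volunteers will seem harmed. With 13 independent two-sided indices the model gives 1 − (1−0.0295)¹³ = 32% to 1 − (1−0.0455)¹³ = 45% with at least one out-of-range value at week 1. The protocol does not support using that figure. It names no such panel, red-cell measures and transaminases move together, and the Appendix 2 table as shown has no blood-count or serum creatinine row. This objection stands.
- **Not every index is selected on.** Potassium, calcium, glucose, bilirubin and amylase are graded in Appendix 2 but are not named as entry conditions in 2.4. For them, zero at screening does not follow. This stands.
- **No comparison of screening with post-dose rates is planned.** Section 2.8 lists no laboratory proportion or change as an endpoint. This stands: the protocol does not announce a biased analysis. It leaves no unselected pre-dose result for any analysis to use.
- **Causality is judged individually.** Appendix 1 weighs expectedness and alternative causes as well as timing, and individual screening values remain available. It would therefore be too strong to say that a genuine early effect cannot be recognised.
- **Baseline definitions belong in an SAP.** That is true of the definition, but not of whether the sample is tested. Section 2.7 provides for frozen plasma for serology, but a blood count cannot be recovered from it, and no later chemistry is planned.

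**Conclusion.** The point holds as a limited, inexpensive design weakness. For blood count, liver enzymes and creatinine, the sole pre-dose result is the selection sample, so some rise at weeks 1 and 12 is expected with no vaccine effect. The direction follows from the design. The size rests on assumptions: about 2% to 5% per index outside a two-sided 95% range at week 1, and, for any of the four liver tests, about 6% to 9% above ULN and 0.2% to 2.3% at the Appendix 2 threshold.

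A reader might go further and conclude that all laboratory abnormalities are zero at baseline, or that chance findings must be attributed to BCG. The documents do not support either. The gain from a tested Day 0 sample is an unselected pre-vaccine rate for the group and a proper starting value for within-person change. It will not remove most chance abnormalities in individual volunteers, and how precise the Day 0 rate is depends on the number enrolled.

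**What to change.** In 2.7, put the asterisk on the pre-vaccination sample too. State there that Day 0 is the baseline for laboratory safety and that screening remains the eligibility test. State, in 2.7 or the analysis plan, that the group's out-of-range rates and the within-person changes at weeks 1 and 12 are compared with Day 0. A rule that counts only results worse than Day 0 should not be relied on alone, for the reason shown in step 4 of the working.

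The cost is one extra routine panel per volunteer. No visit or draw is added, and the volume limits still hold: 8 draws × 55 ml = 440 ml, under the 500 ml ceiling. The Day 0 result may arrive after dosing, so it serves as a baseline and not as a further entry check.

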## **2.8 Endpoints**

The occurrence and severity of local side-effects

The occurrence and severity of systemic side-effects

The induction of T cell responses (as measured by an interferon-gamma Elispot assay).

Proliferation assays and cytotoxic T cell assays will be performed on strong CD4+ and CD8+ responses respectively.

## **2.9 Adverse Events**

See Appendix 1.

### ADVERSE EVENTS

#### *1. Definition and Grading Intensity of Adverse Events*

An adverse event is defined as any unintended change in the body structure (signs) or body function (symptoms), whether or not considered related to test product. During the entire study, subjects will be instructed to report all adverse events. All adverse events, whether volunteered, elicited or noted on physical examination, will be recorded throughout the study.

The severity of adverse events will be categorized as follows:

- MILD = Experience that is minor and does not cause significant discomfort to subject or change in activities of daily living (ADLs); subject is aware of symptoms but symptoms are easily tolerated.
- MODERATE = Experience is an inconvenience or concern to the subject and causes interference with ADLs but the subject is able to continue with ADLs.
- SEVERE = Experience significantly interferes with ADLs and the subject is incapacitated and/or unable to continue with ADLs.

#### *2. Criteria for Determining Relationship to Test Product*

The Investigator will make a determination of the relationship of the adverse event to the test product. The relationship to test product of all adverse events will be classified according to the following guidelines:

- NOT RELATED = Data available to clearly identify an alternative cause of the reaction, e.g., hemorrhage due to mechanical injury.
- UNLIKELY
  - Reasonable temporal relation to vaccination, BUT
  - Unlabeled/unexpected reaction, AND
  - The reaction can be reasonably explained by other factors (such as interventions), AND
  - Negative de-challenge, if available, OR
  - No reasonable temporal relation to vaccination.
- POSSIBLE

- Reasonable temporal relation to vaccination, AND
- Labeled/expected reaction, OR
- Unlabeled/unexpected reaction, BUT
- Other factors could have caused or contributed to the reaction (such as subject's clinical state, concomitant therapy, and/or other interventions).
- PROBABLE
  - Reasonable temporal relation to vaccination, AND
  - Labeled/expected reaction, AND
  - The reaction cannot be reasonably explained by other factors (such as the subject's clinical state, concomitant therapy, and/or other interventions).
- HIGHLY PROBABLE
  - Reasonable temporal relation to vaccination, AND
  - Labeled/expected reaction, AND
  - The reaction cannot be reasonably explained by other factors (such as the subject's clinical state, concomitant therapy, and/or other interventions), AND
  - Positive de-challenge, if applicable, AND
  - Positive re-challenge, OR
  - Application/vaccination site reaction.

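### The causality scale has no category for an unexpected reaction away from the vaccination site that fits in time and has no other explanation

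*Protocol*

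**What the plan says.** Appendix 1, section 2 makes the investigator responsible for judging relatedness and applies the scale without exception: "The relationship to test product of all adverse events will be classified according to the following guidelines". The five categories set these conditions.

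- **NOT RELATED**: "Data available to clearly identify an alternative cause of the reaction".
- **UNLIKELY**: timing fits and the reaction is unexpected, but "The reaction can be reasonably explained by other factors (such as interventions), AND" de-challenge is negative where that is available. The alternative branch is "No reasonable temporal relation to vaccination".
- **POSSIBLE**: timing fits and the reaction is expected. Alternatively, "Unlabeled/unexpected reaction, BUT" with the qualifier "Other factors could have caused or contributed to the reaction".
- **PROBABLE**: timing fits, "Labeled/expected reaction, AND" other factors do not reasonably explain it.
- **HIGHLY PROBABLE**: the three PROBABLE conditions, plus positive de-challenge if applicable, plus "Positive re-challenge, OR" a vaccination-site reaction.

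The section has no unclassifiable category and no separate rule for unexpected reactions.

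**The concern.** Expectedness (was this reaction already known?) and causality (did the vaccine produce it?) are different questions, and the scale merges them. The two highest categories are open to known reactions, while an unexpected reaction is sent to categories that presuppose some other cause. That leaves nowhere to put an unexpected reaction for which no other cause exists.

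This profile matters here. Safety is half of the study objective (section 2.1), the volunteers are being revaccinated 10 to 20 years after a first BCG, and systemic side-effects are one of the endpoints (section 2.8). A systemic reaction not seen before is what the safety part of the trial most needs to be able to attribute. Investigators rate events as they arise, so a later analysis plan cannot supply a rating that the scale never offered.

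**Working it through.** No figure in the protocol bears on this point, so the check is logical. The inputs are the five definitions in Appendix 1, section 2.

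**Step 1. The test profile.** Timing fits; unexpected; no clear alternative cause; not reasonably explained by other factors; no other factor that could have contributed; not at the vaccination site.

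| Category | Condition that decides | Met? |
|---|---|---|
| NOT RELATED | clear alternative cause | no |
| UNLIKELY, first branch | reasonably explained by other factors | no |
| UNLIKELY, second branch | timing does not fit | no |
| POSSIBLE, expected branch | expected | no |
| POSSIBLE, unexpected branch | other factors could have contributed | no |
| PROBABLE | expected | no |
| HIGHLY PROBABLE | expected (or site reaction) | no |

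**Step 2. Does the result depend on how AND, OR and BUT are grouped?** The lists have no brackets, so the plausible groupings were varied:

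- UNLIKELY, 2: the final OR opens a separate branch, or is an alternative to negative de-challenge only.
- POSSIBLE, 4: (timing and expected) or (unexpected and other factors); timing and [expected or (unexpected and other factors)]; timing and other factors, whatever the expectedness; [(timing and expected) or unexpected] and other factors.
- HIGHLY PROBABLE, 2: the final OR stands alone, or is an alternative to re-challenge only.

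This gives 2 × 4 × 2 = 16 groupings. Negative de-challenge, positive de-challenge and positive re-challenge were each set to met and not met, giving 2 × 2 × 2 = 8 settings per grouping and 16 × 8 = 128 cases. In all 128, the non-site profile meets 0 of 5 categories. Positive re-challenge does not help, because for a non-site event HIGHLY PROBABLE still requires an expected reaction.

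**Step 3. The same profile at the vaccination site.** If the final OR stands alone, being a site reaction is sufficient and the event is HIGHLY PROBABLE: 8 of 16 groupings. If the OR replaces only re-challenge, expectedness is still required and no category fits: the other 8.

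**Step 4. The comparator.** Change only unexpected to expected in the non-site profile. The PROBABLE conditions are then met. Two events with the same timing and the same absence of another cause are treated differently solely because one was already known.

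**Step 5. Secondary points.**

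- *Overlap.* An unexpected event that fits in time and that other factors reasonably explain meets the core of UNLIKELY. Factors that explain an event could also have caused it, so it meets POSSIBLE too. Negative de-challenge might separate the two, but it counts only if available, and a single injection on Day 0 (section 2.7) cannot be withdrawn.
- *Re-challenge.* De-challenge in HIGHLY PROBABLE is qualified by *if applicable*; re-challenge is not, although the trial gives one injection.

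**The case against.** The strongest reply is that little in the protocol turns on the causality class. All adverse events are recorded whether or not they are thought related (Appendix 1, section 1). The serious reportable list uses no causality criterion (Appendix 1, section 3), nor does withdrawal for a serious adverse event (section 2.6). This stands, and it limits the consequence. A reader might infer that a new harm would be lost, or that a table of related events would be biased towards reassurance. The protocol supports neither: it specifies no such table, does not say which classes count as related, and does not tie the side-effect endpoints to the scale.

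A reader might also infer that no unexpected event can rate above POSSIBLE. That is too strong, because an unexpected site reaction is HIGHLY PROBABLE if the final OR stands alone.

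Nor does the overlap cover every unexpected event with some conceivable other cause. UNLIKELY asks that other factors reasonably explain the event; POSSIBLE asks only that they could have caused or contributed to it. The wording can separate a merely possible cause from one that explains the event, so the overlap is certain only for the latter.

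On re-challenge, every volunteer has had BCG before, so the trial injection might itself be called a re-exposure. The section does not say whether it counts. An expected systemic event that misses HIGHLY PROBABLE can still be PROBABLE. This remains a minor wording point.

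Finally, the criteria are called guidelines and the investigator decides. That makes misclassification less certain, but does not close the gap: for this profile every available choice departs from the written conditions.

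**Conclusion.** The gap is real for adverse events away from the vaccination site that fit in time, are unexpected and have no other explanation. None of the five categories fits, under any of the 16 groupings and whatever the de-challenge or re-challenge result. For vaccination-site reactions, the answer depends on an OR whose scope the text does not fix.

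The effect is limited to the attribution of new systemic reactions. They can be rated only by going against the text or by supposing another cause. How many such events will occur cannot be stated from the protocol, and one need not occur at all. The overlap of UNLIKELY with POSSIBLE and the unqualified re-challenge condition are secondary.

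The conclusion assumes only that the definitions are applied as written. Because recording, serious-event reporting and withdrawal do not use the scale, this is a should-fix rather than a must-fix.

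**What to change.** Reword Appendix 1, section 2:

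1. Remove labelled/expected status from every causality definition and record it as a separate yes/no field. An event that fits in time and is not reasonably explained by other factors then meets PROBABLE, expected or not.
2. State the scope of the final OR in HIGHLY PROBABLE: whether a vaccination-site reaction is sufficient alone or only replaces re-challenge.
3. Qualify re-challenge with *if applicable*, as is already done for de-challenge.
4. Make UNLIKELY and POSSIBLE exclusive: UNLIKELY where another cause is more likely, POSSIBLE where another cause is possible.

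Adding one clause for the missing profile would close the gap alone, but would leave expectedness and causality mixed. The full change costs one reworded appendix section and one extra case report form field. It alters no dose, visit or procedure.
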